**Study flow chart:**

CP child -caregiver pairs

Normal

>-1SD WHZ, WAZ, HAZ

Malnourished

Screening

**Severe (exclusion)**

MUAC <11.5cm (Child),

<-3SD with Oedema

**Malnourished (inclusion)** N=124

<-2SD WHZ, HAZ, WAZ, MUAC

CURIE-No PFT control cluster

CURIE-PFT intervention cluster

-Caregiver counselling on immediate management of severe malnutrition

-Referral for management

Allocation and randomization

Follow-up

**Study Implementation plan:**

This study and preceding qualitative assessments will be implemented as follows: In the first month, a situation analysis (nutrition survey) will be conducted by trained data collectors or clinicians to identify well-nourished and malnourished children and adolescents with CP from selected organizations in the study area. In order to identify the unique practices of caregivers of well-nourished CP children identified from the nutrition survey, that set them apart from others within the same community, a qualitative survey will be conducted during the second month. From this qualitative survey, a Positive Deviance Inquiry (PDI) report that documents the identified successful practices and good foods will be generated. Based on the PDI report, a positive deviance (PD) program will be designed and evaluated against the Akwenda/CURIE caregiver training program (parent facilitator trainings -PFT) among malnourished CP children through a randomized clinical trial. The trial will be implemented for 3 months. Monthly Nutrition Education and Rehabilitation Sessions (NERS) for identified malnourished children and their caretakers under the PD program, and training sessions under the PFT program will be conducted concurrently. Monthly growth monitoring of all children in the study group will be done by an external team of assessors. In order to evaluate the main effect of the PD program and the PFT programs separately and in conjunction, data management, analysis and reporting will be done in the subsequent months.

**Table 1: A 2x2 table showing the allocations of the different experimental conditions in a factorial design.**

|  | PD-Yes | PD-No |
| --- | --- | --- |
| PFT-Yes | 31 (PFT-Yes, PD-Yes) | 31(PD-No, PFT-Yes) |
| PFT-No | 31 (PFT-No, PD-Yes) | 31 (PD-No, PFT-No) |
|  | 62 | 62 |

**7.0 Ethical Considerations**

Ethical approval for conducting the intervention study was obtained from Makerere University School of Public Health Higher degrees and Research Ethical Committee, and from the Uganda National Council of Science and Technology. Ethical approval for this study protocol will be sought from the same ethics institutions. The trial will be conducted according to the Declaration of Helsinki guidelines.

At the beginning of the surveys, all study participants aged 18 years and above will provide written informed consent. Child participants aged 8 years and above who are able to understand what the study is about will be taken through the assent process. For younger children, care givers will provide informed consent as participant proxies.

Every step will be taken to ensure confidentiality of data obtained. All collected data will be kept on a secure, encrypted laptop and accessed only by the study staff. Each survey will be given a unique identifier and no identifying information will be recorded. Risks and benefits of the study will be explained as outlined in the consent forms.

**COVID-19 risk management plan**

Infection control measures to minimize the risk of Covid-19 among the study team and participants will be implemented as per section 12 of the National guidelines for conduct of research during corona virus disease 2019 pandemic (July 2020) <https://www.uncst.go.ug/guidelines-and-forms/>. These measures include:

1. **Infection Control Measures at Research Institutions or Recruitment Entry**

**Points**

i). All persons presenting at the research institutions or recruitment site entry points should

wash their hands with soap and water or hand sanitizer that is provided at the entry

point.

ii). Screening of research teams and participants with an infrared temperature monitor at

research institutions or recruitment entry points.

iii). When screening/ examining research participants, the person in charge should have

appropriate Personal Protective Equipment (PPE) including a medical mask, gloves, gown

and eye protection (goggle or face shield) to protect themselves.

iv. Persons identified to have temperature≥37.5 C or respiratory/flu-like symptoms and/ or

history to an area with reported community transmission in the last 14 days before the

onset of symptoms (suspected/probable case), once identified shall be referred to district COVID-19 Taskforce teams.

**b). Physical Distancing**

i). A distance of a minimum of two (2) meters should be ensured during research procedures and activities to prevent person- to- person spread of the Corona Virus.

ii). No more than ten (10) people should converge in one place to undertake research

procedures. It is recommended that research teams ensure at least two (2) square meters

for each person. Research teams should avoid hand-shakes and hugging at all times.

**c). Handwashing and Disinfection**

Research teams and participants should consistently wash their hands with soap and water or use a hand sanitizer throughout the day when at the research institutions or recruitment sites until when they are ready to leave.

**d). Use of Personal Protective Equipment for Corona Virus Disease Prevention**

Personal Protective Equipment should be made available to all members of the research team that require it for their duties at the research sites. PPE for Coronavirus disease include gloves, medical/ surgical masks, goggles or face shield, gowns, aprons and medical grade gumboots. The use of PPE in the respective situations or risk categories will be tailored to the current guidelines of Ministry of Health.

**8.0 Study strengths and limitations**

To the best of our knowledge, this is the first experimental study to test the effect of the positive deviance strategy on the nutritional status of children and youth with CP in low-income countries (LICs). The other strength of this study is that the use of home visiting for data collection will allow for a naturalistic assessment of need and observation of the opportunities and barriers the caregiver may face with regards to feeding a child with CP. This will enable the immediate demonstration of advice ‘in situ’, and also help to build trust between the researchers and the families. However, this study had some limitations. Participant selection was primarily within the existing Akwenda/CURIE study two arm structure, and thus allocation of participants to study conditions was not completely random, which increased the potential for non-equivalent study groups and a high risk of bias. However, the difference in groups observed in some baseline factors was adjusted for during statistical analysis to determine the independent main effects of the PD and PFT interventions.

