**Sample size estimation:**

1. **Sample size estimation in a between subjects 2x2 factorial design (Bonnet,2016)**

**
[figure not shown]
**

In order to estimate a main effect in a between-subjects 2x2 factorial design at 95% confidence, at desired confidence interval width of 2.0, and a planning value of 8.0 for the average within group error variance, the contrast coefficients are 0.5, 0.5,-0.5 and-0.5, and the sample size required per group is approximately 31.

1. **Sample size estimation using two proportions:**

The PD program has been reported to increase weight of ≥200g in 12 days among 87% of participants in Burundi [^10^](#_ENREF_10). Based on the prevalence of malnutrition (<-2sd in any of HAZ,WAZ,BMIZ) among the CURIE CP population based cohort reported as 64% as per the 2015 assessments. Assuming the previously reported effect of the PD program, we hope to reduce malnutrition in the CP child population to about 29%, at α =0.05, and power (1-β) =0.8. After imputing these parameters into a Stata program to estimate sample size for individual randomization, of a two proportions test, the estimated total sample size is 62: Hence 31 participants per each of the four arms. Therefore for a 2x2 factorial trial, assuming a 1:1:1:1 allocation, 124 participants will be required for the study with 32 participants in each of the four conditions.

Participants in this study will include eligible caregivers of children with CP participating in the wider CURIE intervention study (Akwenda). In order to account for those that may not be malnourished from the CURIE study sample, additional caregivers of malnourished children with CP will be recruited from community-based organizations (CBOs) operating within the study setting including EKISA ministries and MUSANA community health centre. The CURIE intervention study has got two arms (PFT and Control) separated as village clusters based on geographical proximity and balanced by age, and GMFCS level. This study will utilize the available CURIE intervention clusters to avoid contamination. Details of participant recruitment from different CBOs are displayed below.

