**Data collection:**

The data collection team will consist of a clinician to take anthropometric assessments, therapists to assess for CP severity, research assistants equipped with skills in data collection, and community mobilisers chosen from the catchment districts.

Once the caregiver-child pairs are enrolled, the research assistants will use a designed locally translated structured questionnaire to record identifying and demographic data: i) the child’s demographics, feeding difficulties, other reported health conditions and recorded anthropometry ii) the primary caregiver’s socio-demographic and economic characteristics. Severity of cerebral palsy will be assessed by trained therapists using the Gross Motor Function Classification System[^20^](#_ENREF_20). Feeding difficulties will be assessed based on parent /caregiver reports using on responses to questions on feeding extracted from an informal questionnaire previously designed by the CURIE study for clinical assessments. Parental/caregiver reports have historically been used as a measure of feeding and or oral motor status in individuals with CP.

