**Data management and analysis.**

Descriptive statistics will be performed by tabulation of the summary means of the individual condition levels and baseline social demographic characteristics of the children and their caregivers. Participants’ characteristics will be presented in frequency tables. A two-way analysis of variance (ANOVA) will be performed to test the independent main effects of PD and PFT, and the effect of interaction of both PD and PFT. Factor levels will be compared by a pairwise comparison of treatment means (standard error of a difference) or a fisher’s least significant difference (LSD) test. This analysis will be done in both intention to-treat and per-protocol assumptions. All analysis will be expressed in 95% two sided confidence intervals and a p-value of <0.05 will indicate statistical significance.

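### Covariates are to be picked by observed baseline difference, while the stated ANOVA has none: reconcile the two and fix prognostic covariates in advance

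*Protocol*

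**What the plan says.** Three places in the protocol bear on this.

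- **Data management and analysis.** "A two-way analysis of variance (ANOVA) will be performed to test the independent main effects of PD and PFT", together with their interaction. No covariate is mentioned. The same section adds that "All analysis will be expressed in 95% two sided confidence intervals and a p-value of <0.05 will indicate statistical significance".
- **8.0 Study strengths and limitations.** After conceding that allocation was not fully random and carried a high risk of bias, the protocol offers as remedy that "the difference in groups observed in some baseline factors was adjusted for during statistical analysis to determine the independent main effects". It names no factors, and gives no test or threshold for calling a difference observed.
- **Randomization and blinding.** CURIE participants are randomised to PD or no PD within each existing CURIE arm. PFT follows the CURIE village groups, which are geographic and were matched on age, sex and motor function. Recruits from other organisations join the PFT or control side according to where they live.

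The likely prognostic variables are already recorded. Weight, age and sex are needed for the Z-scores. Under Data collection, "Severity of cerebral palsy will be assessed by trained therapists using the Gross Motor Function Classification System", and the questionnaire covers feeding difficulties and the caregiver's socio-demographic and economic characteristics.

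**The concern.** The first problem is a mismatch: one section describes an analysis without covariates, the other an adjusted one. A reader cannot tell which produces the main result.

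The second is the selection rule. Whether groups differ on a factor at baseline and whether that factor predicts the outcome are separate questions.

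- **PD.** Among those randomised, baseline differences are chance. A strong predictor that happens to look balanced stays out of the model, and the precision it would have bought is lost.
- **PFT.** Allocation is by place, so real differences are possible. A small or moderate one may not stand out with 62 children per side and would go unadjusted. Age, sex and motor function, balanced by matching, are the factors such a rule is most likely to omit.

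At stake are the width of the PD confidence interval and a modest part of the PFT bias that section 8.0 says was dealt with.

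**Working it through.** **The plan's own figures.** The inputs are "at desired confidence interval width of 2.0, and a planning value of 8.0 for the average within group error variance", and "the contrast coefficients are 0.5, 0.5,-0.5 and-0.5, and the sample size required per group is approximately 31".

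- Confidence-interval route: n = 4 × variance × Σc² × (z/w)² = 4 × 8 × 1 × (1.96/2)² = 30.7, so 31 per cell. Reproduced.
- Two-proportion route: malnutrition "reported as 64% as per the 2015 assessments", and "we hope to reduce malnutrition in the CP child population to about 29%, at α =0.05, and power (1-β) =0.8". With p̄ = 0.465, n = [1.96√(2 × 0.465 × 0.535) + 0.842√(0.64 × 0.36 + 0.29 × 0.71)]² / 0.35² = 30.7, so 31 per group. Reproduced.

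With 31 per cell each main effect compares 62 with 62. The standard error in SD units is √(2/62) = 0.180.

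**Assumptions not in the protocol.** One continuous covariate with correlation r to a continuous outcome; an effect of about 0.5 SD (80% unadjusted power corresponds to 0.503 SD, or 1.42 units at variance 8); a difference counts as observed when p<0.05.

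**PD, fixed adjustment.** The residual SD shrinks by √(1 − r²).

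- Power ≈ Φ(0.5 / (0.180√(1 − r²)) − 1.96), which gives about 83% at r = 0.3, 89% at r = 0.5 and 93% at r = 0.6.
- On the plan's own scale, the interval width is 2 × 1.96 × 2.83 × 0.180 × √(1 − r²): 1.99 unadjusted and 1.72 at r = 0.5.

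**PD, selection by observed difference.** A truly balanced factor enters the model in only about 4-5% of trials. Simulated power with 31 per cell is then about 80-82%, barely above no adjustment. The test is slightly conservative, with a size of about 4%.

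**PFT, chance that a real imbalance is flagged** (noncentral t, 62 v 62, two-sided 5%):

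| True imbalance (SD) | 0.2 | 0.3 | 0.355 | 0.4 | 0.5 | 0.8 |
|---|---|---|---|---|---|---|
| Flagged | 20% | 38% | 50% | 60% | 79% | 99% |

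The 50% point moves to 0.30 SD with a 10% threshold and 0.23 SD with a 20% threshold.

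**PFT, what each approach leaves behind** (2x2 simulation, 3,000 trials per setting, r = 0.5, no true PFT effect, imbalance tested between the PFT sides):

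| True imbalance | Bias (SD): never adjust / rule / fixed | Type I error: never adjust / rule / fixed |
|---|---|---|
| 0.2 SD | 0.10 / 0.05 / 0.00 | 7.4% / 5.3% / 5.7% |
| 0.3 SD | 0.15 / 0.06 / 0.00 | 13.8% / 5.5% / 5.0% |
| 0.5 SD | 0.25 / 0.03 / 0.00 | 27.9% / 5.7% / 5.0% |

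A larger run (20,000 trials) gives 0.058 SD and 6.0% for the rule at 0.3 SD. If the imbalance is judged by a four-group F test instead, the rule leaves 0.09 SD and 7.8% there.

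**The case against.** **Thin evidence of a plan.** The sentence in section 8.0 is a past-tense remark among limitations. It does not say that only differing factors were adjusted for, and covariate lists often sit in an SAP, which is not shown here. This stands as a caution. The point is therefore not that a list is missing: the protocol states one basis for choosing covariates, and that basis is poor and disagrees with its own analysis section. It also cannot be inferred that covariates were chosen with outcomes in view. Baseline anthropometry is recorded at enrolment, and differences can be judged without follow-up data.

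**Stronger readings that the documents do not support.**

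- A reader might infer that PFT carries a 0.15 SD bias and about 13% type I error at a 0.3 SD imbalance. Those figures describe never adjusting. The rule catches the larger realised imbalances and leaves far less.
- A reader might infer that confounders are generally missed more often than found. That holds only below about 0.355 SD under an assumed 5% test, and the protocol gives neither a threshold nor an imbalance size.
- A reader might infer that adjustment by this rule never helps PD. When a prognostic factor enters because the PFT sides differ, PD power rises too, to about 85-89% at imbalances of 0.35-0.8 SD.

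**Size of the gain.** The correlations are assumed, and at 0.3 the gain is only a few points. The primary outcome is worded as thresholds of weight gain, whereas the calculation fits the continuous ANOVA. Both limits stand.

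**Whether the remedy reaches PFT.** Age, sex and motor function were already matched, so fixing only those would do little for differences between places. That is right, and it is why the fix adds feeding difficulties and caregiver socio-economic characteristics.

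**Conclusion.** The concern holds in a limited form. The analysis section and section 8.0 describe different models and must be reconciled. Selection by observed difference is a poorer basis than a set fixed on prognostic grounds.

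The main cost is PD precision for factors that look balanced: roughly 1 to 13 percentage points of power across correlations of 0.3 to 0.6 (80-82% against 83-93%). The PFT harm is smaller: a residual bias of about 0.06 SD and type I error of about 6% at a 0.3 SD imbalance in a measured factor with correlation 0.5.

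These sizes rest on a continuous outcome, a 0.5 SD effect, a 5% imbalance test and the assumed correlations. The mismatch between sections rests on none of them.

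**What to change.** In Data management and analysis, state that every main-effect and interaction model includes the same covariates, fixed before follow-up data are seen and kept whether or not the groups differ:

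- baseline weight or Z-score, age, sex and GMFCS level;
- because PFT is allocated by geography, feeding difficulties and caregiver socio-economic characteristics, entered as a small number of terms.

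Reword section 8.0 to refer to this set, and label any covariate added after looking at the data as a sensitivity analysis.

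The change is one of wording, with no new data or participants. It uses a few of the 124 − 4 = 120 residual degrees of freedom of the four-cell model. It does not remove unmeasured geographic confounding of PFT, and section 8.0 should continue to say so.
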